### Sensitivity Models

#### Multiple Testing

Given the need for multiple models to be fitted within each study, the GLAD Taskforce recommends a *P* value adjustment procedure, such as the Simes method, to minimize the chance of a type 1 error and determine whether multiple testing may be influencing results [32]. This should be applied to all models in a study where multiple models are required.

#### Outliers and Influential Data

Initial models include all available data points, with sensitivity analyses included for any influential or outlying observations. Influential observations are determined by predicting residuals, Cook’s distance, or DFBETA after fitting the relevant model. Although several cutoff points have been proposed to identify influential observations, conventional cutoffs are applied: 3 for standardized residuals [33]; 4/(n-p) for Cook’s Distance [34], where n=sample size and p=number of parameters in the model; and 2/√n for DFBETA [35].

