^c^Outcomes must be binary (condition present vs condition absent). For studies that only use symptom scales, validated cutoffs can be used to determine condition present versus condition absent (refer to Multimedia Appendix 1).

^d^*DSM-IV-TR*: *Diagnostic and Statistical Manual of Mental Disorders (Fourth Edition, Text Revision)*.

^e^*ICD-10*: *International Statistical Classification of Diseases, Tenth Revision*.

^f^MDD: major depressive disorder.

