#### Estimating Risk Ratios, Odds Ratios, and Hazards Ratios

Each study is required to use risk ratios (estimated by Poisson regression with robust SE) as the primary means of assessing the association of dietary intake with CMDs. Risk ratios are based on incident cases, and so models will need to exclude participants with depression or anxiety at baseline. Furthermore, to determine incident risk, studies must have dietary exposures at baseline and depression, or anxiety measured at a subsequent time point. Where the estimation of a risk ratio is not possible (refer to Figure 2), for example, where the total number of people exposed at baseline is not available (such as for retrospective or case-control studies) [29], odds ratios are estimated using standard logistic regression techniques. Where only time-to-event data are available, hazard ratios are used, estimated by a Cox proportional hazards model. For rigor, all effect estimates will be accompanied by a 95% CI and exact *P* value [30].

Models can be fitted using any statistical analysis software, including R (R Core Team), SAS/STAT (SAS Institute Inc), Stata (StataCorp LLC), and SPSS (IBM Corp). Before fitting the relevant models, Member studies must assess model assumptions. Should any model assumptions be violated, an alternate approach to analysis may be selected. For example, the nonlinearity of continuous variables should be investigated, and transformations or nonlinear models fitted where necessary. Similarly, should any of the assumptions of Cox proportional hazards models be violated, alternative strategies will be deployed to account for these violations.

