**Figure 2 figure2:**
[figure not shown]
The types of ratio measures that can be obtained from binary outcome data. Odds ratios will be estimated using logistic regression, risk ratios will be estimated using Poisson regression with robust SE, and hazard ratios will be estimated using Cox regression.

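### The outlier and influence cutoffs are linear-regression rules; in the required Poisson and logistic models they mainly pick out who became a case, so an exclusion-based sensitivity analysis would mislead

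*Protocol article*

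**What the plan says.** The Outliers and Influential Data section of the Protocol article, under Sensitivity Models, sets the general approach: "Initial models include all available data points, with sensitivity analyses included for any influential or outlying observations". Such records are identified from residuals, Cook's distance "or DFBETA after fitting the relevant model". The thresholds are then fixed: "conventional cutoffs are applied: 3 for standardized residuals [33]; 4/(n-p) for" Cook's distance, and 2/√n for DFBETA. The section does not name the residual type or the coefficient to which DFBETA refers. It also does not say what is done with a flagged record.

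The models that these thresholds apply to are fixed elsewhere:

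- Table 2, footnote c: "Outcomes must be binary (condition present vs condition absent".
- The section Estimating Risk Ratios, Odds Ratios, and Hazards Ratios sets the main model: "Each study is required to use risk ratios (estimated by Poisson regression with robust SE) as the primary means". It then restricts who enters that model: "Risk ratios are based on incident cases, and so models will need to exclude participants with depression or anxiety at baseline".
- The same section, where a risk ratio cannot be obtained: "odds ratios are estimated using standard logistic regression techniques", with Cox regression where only time-to-event data exist. The Figure 2 legend repeats this: "Odds ratios will be estimated using logistic regression, risk ratios will be estimated using Poisson regression with robust SE".

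**The concern.** With a continuous, roughly normal outcome, a standardized residual beyond 3 is rare and marks an odd record. With a 0/1 outcome the residual has only two possible values at a given fitted risk. When that risk is low, the value for a case is large simply because the event occurred. Cook's distance and DFBETA carry the same residual, so they inherit the problem. Removing baseline cases pushes the outcome proportion down, which makes it worse.

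At stake is a check that every member study is asked to run. If flagged records are left out, the refit either has no events or keeps mainly the cases that already agree with the fitted trend. The first cannot be analysed. The second exaggerates the association and could be taken as support for the project's hypotheses. The choice among three diagnostics also weakens harmonization, because compliant studies can flag very different sets of people.

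**Working it through.** **Inputs.** From the documents: the cutoffs 3, 4/(n-p) and 2/√n; a binary outcome; Poisson or logistic models; baseline cases excluded; cohort sizes from 639 to 171,000; and the Model 2 covariates age, sex and socioeconomic status. Assumed: incidence 2 to 30%, p = 5 parameters including the intercept, a skewed exposure, and a log RR of about -0.10 per SD. The plan states no figure of its own on this point, so there is none to reproduce.

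**Closed form, residual cutoff.** Let μ be the fitted risk.

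- Poisson Pearson residual of a case: (1-μ)/√μ. Setting this above 3 gives √μ < (√13-3)/2 = 0.303, so μ < 9.2%.
- Logistic Pearson residual of a case: √((1-μ)/μ) > 3 gives μ < 10%.
- Non-cases: the Poisson value is -√μ, which cannot reach -3 for a risk. The logistic value is -√(μ/(1-μ)), which passes -3 only if μ > 90%.
- Poisson deviance residual of a case: √(2(-ln μ-(1-μ))) > 3 only if μ < 0.41%. Logistic: √(-2 ln μ) > 3 only if μ < e^(-4.5) = 1.1%.

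**Closed form, Cook's distance.** D = r²h/(p(1-h)²). At average leverage h = p/n this is about r²/n, so D > 4/(n-p) means roughly |r| > 2. For a case that gives μ < (√2-1)² = 17.2% (Poisson) or μ < 20% (logistic).

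**Simulation.** Share of cases flagged in Poisson models, nearly constant over n = 639, 3,000, 24,325 and 100,000:

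| Incidence | Pearson > 3 | Cook > 4/(n-p) | DFBETA, exposure | DFBETA, any coefficient |
|---|---|---|---|---|
| 2% | 98-100% | 100% | about 78% | 99-100% |
| 5% | 90-99% | 100% | about 63% | 99-100% |
| 8% | about 60% | 96-98% | about 52% | 99-100% |
| 10% | 30-38% | about 88% | about 45% | 99-100% |
| 15% | about 4% | about 48% | about 30% | 81% |
| 20% | 0% | 21% | 18% | 70% |
| 30% | 0% | 4% | 8% | 43% |

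Deviance residuals above 3 occurred in 0 to 2% of cases at every incidence. Among non-cases, Cook's distance flagged 0 to 0.1%, exposure DFBETA under 1%, and DFBETA on any coefficient at most about 2.6%. Logistic results were similar or slightly higher (Cook's distance: 100% of cases at 5%, about 93% at 10%, about 35% at 20%). The logistic deviance residual reached 10% of cases only at 2% incidence with n = 639.

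**Effect of excluding flagged records (Poisson, n = 24,325).** At 5% incidence or less, Cook's distance leaves no events. At 10%, 2,427 cases fall to 278. Where a refit is possible:

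- 15% incidence: log RR per SD -0.122 becomes -0.418 with Cook's distance (0.418/0.122 = 3.4 times) and -0.356 with exposure DFBETA (2.9 times). As risk ratios, 0.89 becomes 0.66 or 0.70.
- 20% incidence: -0.102 becomes -0.316 (3.1 times) or -0.379 (3.7 times). As risk ratios, 0.90 becomes 0.73 or 0.68.

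The direction is as expected: the cases removed are those with low fitted risk or high leverage, which are the ones that contradict the fitted slope. A second simulation at n = 20,000 gave the same pattern: Cook's distance flagged 100% of cases at 2 to 5%, 97% at 8%, 88% at 10% and 49% at 15%, and after exclusion the log RR was between -0.31 and -0.39 at 15 to 20%.

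**The case against.** A reader might infer that the plan flags essentially every incident case and deletes it. The documents do not support that, for four reasons.

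- **Deletion is not stated.** The section promises sensitivity analyses and keeps all data in the initial models. Excluding and refitting is the usual meaning of such an analysis, but it is an inference.
- **Incidence is not given.** Symptom-scale cutoffs are allowed and the cohorts run from childhood to old age, so incidence may be well above 10% in some. At 20% Cook's distance flags 21% of cases and Pearson residuals none. In case-control data the case fraction is set by sampling and need not be low.
- **The diagnostic matters.** Exposure DFBETA never reached more than about 80% of cases, and a study using deviance residuals would flag almost nobody.
- **The reach is limited.** The primary estimate is untouched, the meta-analysis has its own later protocol, and nothing says that these sensitivity estimates will be pooled.

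It can also be said that an article leaves such detail to a fuller plan. That does not answer the point: the cutoffs are stated as applied, and the Results section has member studies follow the analysis plan given in this paper. The first three objections limit how far the claim goes. They do not rescue the rule, because the distortion at 15 to 20% incidence arises where far from all cases are flagged. The freedom to choose a diagnostic is itself a harmonization problem: at 5% incidence compliant studies could flag 100%, about 63%, or 0 to 2% of cases.

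**Conclusion.** The concern holds in limited form. The stated cutoffs are unsuited to Poisson and logistic models of a binary incident outcome, where they identify mainly who became a case and not aberrant data. The share of cases flagged ranges from nearly all (Cook's distance up to about 8% incidence, Pearson residuals up to about 5%, DFBETA on any coefficient up to about 10%) to almost none (deviance residuals). If flagged records are excluded, the robustness check has no events under Cook's distance at 5% incidence or less. At 15 to 20%, Cook's distance or exposure DFBETA overstates the log RR about three- to fourfold.

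These sizes rest on assumed incidence, five parameters and a modest effect, and on exclude-and-refit as the handling. Cox models were not tested, so no size is claimed for them. A reader should not conclude that the primary risk ratios are affected. The section should be corrected, but the fault lies in a secondary check and does not undermine the main analysis.

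**What to change.** In Outliers and Influential Data, state for binary-outcome models that:

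1. No record is excluded because it crosses a residual, Cook's distance or DFBETA cutoff.
2. The exclusion sensitivity analysis uses exposure-side criteria fixed in advance and applied without regard to outcome: implausible total energy intake, extreme intake values, or high leverage.
3. DFBETA is used descriptively only, to rank observations for data checking and to report the largest change in the exposure coefficient, without a 2/√n deletion rule.

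The cost is a small amount of rewording. The one real task is to agree the exposure thresholds across member studies, whose dietary instruments and age ranges differ.

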Fruits	Average daily consumption of less than 310-340 g of fruit including fresh, frozen, cooked, canned, or dried fruit, excluding fruit juices and salted or pickled fruits.	grams/day
Vegetables	Average daily consumption of less than 280-320 g of vegetables, including fresh, frozen, cooked, canned, or dried vegetables and excluding legumes and salted or pickled vegetables, juices, nuts and seeds, and starchy vegetables such as potatoes or corn.	grams/day
Legumes	Average daily consumption of less than 90-100 g of legumes and pulses, including fresh, frozen, cooked, canned, or dried legumes.	grams/day
Whole grains	Average daily consumption of less than 140-160 g of whole grains from breakfast cereals, bread, rice, pasta, biscuits, muffins, tortillas, pancakes, and other sources.	grams/day
Nuts and seeds	Average daily consumption of less than 10-19 g of nuts and seeds.	grams/day
Milk	Average daily consumption of less than 360-500 g of milk including non-fat, low-fat, and full-fat milk, excluding plant derivatives.	grams/day
Red meat	Any intake of red meat including beef, pork, lamb, and goat but excluding poultry, fish, eggs, and all processed meats.	grams/day
Processed meat	Any intake of meat preserved by smoking, curing, salting, or addition of chemical preservatives.	grams/day
Sugar-sweetened beverages	Any intake of beverages with ≥50 kcal per 226.8-g serving, including carbonated beverages, sodas, energy drinks, and fruit drinks, but excluding 100% fruit and vegetable juices.	grams/day
Fiber	Average daily consumption of less than 21-22 g of fiber from all sources including fruits, vegetables, grains, legumes, and pulses.	grams/day
Calcium	Average daily consumption of less than 1.06-1.1 g of calcium from all sources, including milk, yogurt, and cheese.	grams/day
Seafood omega-3 fatty acids	Average daily consumption of less than 430-470 mg of eicosapentaenoic acid and docosahexaenoic acid.	milligrams/day
Polyunsaturated fatty acids	Average daily consumption of less than 7%-9% of total energy intake from polyunsaturated fatty acids.	total percentage of daily energy intake
Trans fatty acids	Any intake of trans fat from all sources, mainly partially hydrogenated vegetable oils and ruminant products.	total percentage of daily energy intake
Sodium	Average 24-hour urinary sodium excretion greater than 1-5 g.	grams/day

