Ultra-processed foods (optional)	Any intake of ultraprocessed foods, as defined by the Nova system as any food item in Nova category 4 (“ultraprocessed food”), in grams [20].	grams/day

^a^Based on the GBD (Global Burden of Diseases, Injuries, and Risk Factors Study) risk exposure definitions (Pages 217-218 in Supplementary Appendix 1 in the study by the the GBD 2019 Risk Factors Collaborators [19]).

^b^GBD: Global Burden of Diseases, Injuries, and Risk Factors Study.

^c^Analyses using continuous exposures are required by the GLAD Taskforce. The units listed here are recommended, however, these may be rescaled to more meaningful units in papers (eg, per 10 g) provided the original units are available to the project team.

**Table 2 table2:** Mental health definitions and recommended coding for the GLAD^a^ project^b^.

Mental disorder	Outcome definition	Diagnostic reference	Recommended coding^c^
Major depressive disorder	Involves the presence of at least one major depressive episode, which is the experience of either depressed mood or loss of interest/pleasure, for most of every day, for at least two weeks.	DSM-IV-TR^d^: 296.21–24; 296.31–34. ICD-10^e^: F32.0-9; F33.0-9.	0=no MDD^f^; 1= MDD
Anxiety disorders (any subtype)	Involves experiences of intense fear and distress, typically in combination with other physiological symptoms. Anxiety disorders will be modeled as a single cause for “any” anxiety disorder to avoid the double-counting of individuals meeting criteria for more than one anxiety disorder. Epidemiological estimates reporting an outcome for “any” or “total” anxiety disorders will be included if they reported on at least three anxiety disorders.	DSM-IV-TR: 300.0-300.3; 208.3; 309.21; 309.81. ICD-10: F40-42; F43.0; F43.1; F93.0-93.2; F93.8.	0=no anxiety disorder; 1=anxiety disorder

^a^GLAD: Global burden of disease Lifestyle And mental Disorders.

^b^The definitions and diagnostic references presented in this table are the current definitions used by the GBD (Page 4 in the Supplementary Appendix in the study by the GBD 2019 Mental Disorders Collaborators [1]). Since GLAD members may use alternative methods to ascertain disorder status, definitions or diagnostic references may vary slightly. For example, somatic forms of depression may be captured more by symptom scales, or studies using prescriptions may use Anatomical Therapeutic Chemical codes to determine incident depression and anxiety.

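### The 2/√n cutoff is paired with unscaled DFBETA; it fits only DFBETAS, so read literally the influence check depends on the unit in which diet is coded

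*Protocol article*

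**What the plan says.** All in the protocol article.

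- **Role of the check** (Outliers and Influential Data): "Initial models include all available data points, with sensitivity analyses included for any influential or outlying observations". The main model therefore keeps everyone.
- **Diagnostics** (same section): residuals, Cook's distance or DFBETA, offered as alternatives.
- **Cutoffs** (same section): "conventional cutoffs are applied: 3 for standardized residuals [33"; then 4/(n-p) for Cook's distance, "where n=sample size and p=number of parameters in the model; and 2/√n for DFBETA [35". The residuals are called standardized. No scaling is stated for DFBETA.
- **Exposure scale** (Table 1, footnote c): "Analyses using continuous exposures are required by the GLAD Taskforce". Most exposures are coded in g/day, omega-3 in mg/day and two fats as % of energy. Footnote c adds that "these may be rescaled to more meaningful units in papers (eg, per 10 g"), provided the project team can obtain the original units.
- **Numeric size of the coded values** (Table 1): calcium, in g/day, is defined by "Average daily consumption of less than 1.06-1.1 g of calcium from all sources"; omega-3, in mg/day, by "Average daily consumption of less than 430-470 mg of eicosapentaenoic acid and docosahexaenoic acid".
- **Who applies it**: 18 cohorts with 639 to 171,000 participants (Results), each free to use any statistical software (Estimating Risk Ratios, Odds Ratios, and Hazards Ratios).

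**The concern.** A threshold without units is set against a statistic that has them. Whether a participant counts as influential then depends on whether intake is typed in grams, tens of grams or milligrams, and not only on what that participant does to the estimate. A study that chose DFBETA alone and computed it unscaled could report no influential records for most foods while one implausible intake was moving the coefficient by more than a standard error. The check would also not be comparable between exposures, or between papers that rescale, although harmonization is the purpose of the project. The point concerns scale only. It does not ask whether cutoffs of this kind suit a binary outcome.

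**Working it through.** The plan gives no computed figure to reproduce, only the rule. The cutoff itself is 2/√639 = 0.0791, 2/√3348 = 0.0346, 2/√24,325 = 0.0128 and 2/√171,000 = 0.00484 (sample sizes from Table 4).

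**1. Units.** Let b be the log risk ratio per coded unit and DFBETA_i = b − b(−i). If intake is recoded in units c times larger, b, DFBETA and SE(b) are all multiplied by c. DFBETA changes; DFBETAS_i = DFBETA_i / SE(b) does not.

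**2. Which statistic 2/√n fits.** The squared DFBETA values sum to roughly SE(b)², so the squared DFBETAS sum to roughly 1 and their typical size is 1/√n. A limit of 2/√n is twice that. No such relation holds for the raw statistic.

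**3. What the literal rule demands.** For a Poisson model with a rare outcome, SE(b) ≈ 1/(SDx·√(n·rate)). Raw |DFBETA| > 2/√n then means |DFBETAS| > (2/√n)·SDx·√(n·rate) = 2·SDx·√rate. The sample size cancels.

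The SDs and the 10% incidence below are assumptions, not in the article (√0.10 = 0.316):

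| Exposure and unit | Assumed SD | Bar = 2 × SD × 0.316 |
|---|---|---|
| Fruit, g | 150 | 95 |
| Omega-3, mg | 300 | 190 |
| Fiber, g | 8 | 5.1 |
| Fiber, per 10 g | 0.8 | 0.51 |
| Calcium, g | 0.35 | 0.22 |

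At 2% incidence each bar is multiplied by √(0.02/0.10) = 0.447, so fiber in g falls to about 2.3.

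**4. Simulation without planted errors.** Poisson models adjusted for age and sex; gamma intakes, 10% incidence and log RR −0.1 per SD, all assumed:

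| n | Fruit in g: raw flags | Fruit: DFBETAS flags | Calcium in g: raw flags |
|---|---|---|---|
| 639 | 0 | 28 | 6 |
| 3348 | 0 | 162 | 1 |
| 24,325 | 0 | 1090 | 0 |
| 171,000 | 0 | 7858 | 0 |

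The other simulated food groups and fiber in g, and omega-3 in mg, also had no raw flags at any n. Calcium flags vanish in large cohorts because the bar stays near 0.21 while the largest DFBETAS shrinks: 0.251 at n=3348, 0.103 at 24,325 and 0.039 at 171,000.

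**5. Same data, different unit.** Fruit at n=3348: raw flags 0 per g, per 10 g and per 100 g, 31 per kg and 529 per 10 kg; DFBETAS flags 165 in every coding. Omega-3 at n=639: raw 0 in mg and 6 in g. Calcium at n=639: raw 0 in mg and 6 in g.

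**6. One planted extreme participant with the outcome**, n=639, 10% incidence, 100 runs with exact deletion:

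| Planted intake | Median DFBETAS | RR per SD with / without the record | Raw flag per g | Raw flag per 10 g |
|---|---|---|---|---|
| Fiber 120 g | 1.55 | 1.07 / 0.91 | 0% | 95% |
| Nuts 200 g | 2.59 | 1.08 / 0.91 | 0% | 83% |
| Fruit 2000 g | 1.52 | 1.06 / 0.91 | 0% | 0% |

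Calcium at 4 g/day was flagged in 100% of runs in g and 0% in mg. DFBETAS with the same limit flagged the planted record in 100% of runs in every case.

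In a separate set of single draws, raw DFBETA per g for fiber was 0.0069 at 10% incidence and 0.0335 at 2%. Both are below 0.0791. Ten times these, for per-10-g coding, gives 0.069 (not flagged) and 0.335 (flagged). The flip is common, not certain.

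**The case against.** The strongest reply is that this is a naming slip. The section calls its cutoffs conventional and cites a source, and 2/√n makes sense only for the scaled statistic, so a knowledgeable analyst would compute DFBETAS anyway. That is likely. But the cited source is not available here, and the text is what has to align 18 teams working in different software.

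The second reply also stands. DFBETA is one of three diagnostics joined by *or*. Standardized residuals and Cook's distance do not change when an exposure is rescaled, so a study using either is untouched. Harm needs a study that uses DFBETA alone and computes it raw.

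Third, the article's own rescaling example does not change the result for every food: fruit gave no raw flags per g or per 10 g. It does so for fiber and nuts, whose bar per g is about 5 and per 10 g about 0.5.

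Fourth, naming DFBETAS does not make the check a thorough error detector. In a separate simulation (n=1202, 10% incidence, lognormal fruit intakes) with ten tenfold intake errors planted, raw DFBETA flagged none, and DFBETAS flagged about 3.5 of the ten.

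A reader might infer that the rule can never flag anyone for a gram- or milligram-coded exposure, or that every study following the plan will report no influential records whatever its data. Neither is supported. Table 1 codes calcium in g/day and raw DFBETA does flag it in smaller cohorts, and the plan offers two other diagnostics. Nor can it be said that no exposure is ever flagged at n=171,000; that held only for the intakes simulated.

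**Conclusion.** The concern holds in a limited form. The stated pairing of 2/√n with DFBETA is wrong as written; the cutoff belongs to DFBETAS. That conclusion rests on algebra alone. Taken literally, the rule is practically inert for most food groups and fiber in g/day and for omega-3 in mg/day, active for small-number exposures such as calcium in g/day in smaller cohorts, and sensitive to recoding. The counts and percentages rest on assumed intake distributions and, in the main runs, 10% incidence; lower incidence lowers the bar.

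The consequence is confined to an influence sensitivity analysis in studies that rely on unscaled DFBETA. Primary risk ratios do not change. The correction is worth making because it costs almost nothing and DFBETA is the only one of the three diagnostics aimed at the dietary coefficient itself.

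**What to change.** Replace the DFBETA clause with: |DFBETAS| > 2/√n for the dietary coefficient, where DFBETAS is DFBETA divided by the standard error of that coefficient. Add that raw DFBETA is not to be compared with this limit. It would help to say which standard error is meant (model-based or robust) and that the same definition applies to the Poisson, logistic and Cox models; either standard error removes the dependence on units.

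Cost: a sentence or two in the analysis instructions. No new data are needed, and the standard error is already in the model output. A member study that has already run the check on raw DFBETA would need to divide by that standard error and repeat the flagging and, where the set changes, the sensitivity analysis.
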